### 2.4. Monitoring of the Trial

#### 2.4.1. Data Monitoring Committee (DMC)

Given the anticipated low risk of the IST intervention, the non-pharmacological nature of the trial, its single-arm design and its scale (N = 18), a formal, independent DMC has not been constituted. Monitoring of participant safety and study integrity will be the ongoing responsibility of the principal investigator ([name]) and the research team, including their thesis supervisors ([name] and [name]). Regular team meetings will be held to review progress, adherence and any adverse events reported.

#### 2.4.2. Interim Analyses and Trial Stopping Guidelines

No formal interim analyses of efficacy or futility are planned that would lead to early stopping of the trial. The study will continue until completion of the 17-week follow-up of all participants, unless unforeseen safety concerns warrant an overall reconsideration of the protocol by the principal investigator and the ethics committee, who would make a decision on early termination for safety reasons.

#### 2.4.3. Collection, Assessment, Reporting and Management of Adverse Events (AEs)

Active safety monitoring will be performed throughout the study.

Collection: In each training session, the trainer will actively ask about unusual complaints or symptoms (requested AEs). Participants will be instructed to spontaneously report any AEs between sessions to the principal investigator or trainer. All AEs will be systematically recorded.Assessment: The description, dates, intensity (mild, moderate, severe), seriousness (if Serious Adverse Event—SAE), measures taken and causality (relationship to SAE) of each AE will be documented by the principal investigator and the study doctor. A SAE will be defined as one that results in death, is life-threatening, requires hospitalisation/prolongation of life, results in significant disability/incapacity, or is a congenital anomaly.Reporting: All AEs will be recorded in each participant’s CRF. AEs will be reported to the Research Ethics Committee of the University of Deusto according to its regulations and deadlines.Management: Care will be provided in the event of an AE. If the AE is mild and related to the intervention, a temporary break may be considered (although progression is standardised). If the AE is moderate, severe, or considered a SAE, or if deemed necessary for participant safety by the principal investigator or study doctor, discontinuation of the participant’s involvement will be considered (as detailed in Section 2.1.2). Any participant who suffers harm as a result of trial participation will receive appropriate medical treatment.

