Therefore, the main research question that this protocol seeks to address is whether a 16-week IST programme can be an effective, safe and applicable intervention to counteract sarcopenia and dynapenia and improve quality of life in older adults, and to explore the individual factors that modulate response. Although IST is generally considered safe, potential discomfort or adverse events will be carefully monitored, as detailed in the methodology section (see Section 2.2.2 on safety assessment).

Consequently, the main objective of this study is to design an intervention protocol to evaluate the effect of 16 weeks of IST on sarcopenia, dynapenia and quality of life among adults aged 70 years and above. In addition, the influence of genetic and environmental variables on the variability of response to IST will be analysed in order to optimise its applicability and efficacy in this population group.

With a view to meeting the main objective of the study, a protocol is proposed to achieve the following strategic objectives:To assess the reduction of sarcopenia and dynapenia by increasing muscle mass and strength following the application of an IST protocol in older adults.To analyse the improvement in quality of life following the application of the IST protocol.To assess the applicability of the IST in terms of safety for, and acceptability and perceived difficulty by older adults.To determine the influence of genetic factors on the response to IST, considering variables related to muscle type, fibre damage and regeneration, vascularisation, inflammation, resistance to oxidative damage, and fat and carbohydrate metabolism.

The main hypothesis of the study is that the IST represents a highly effective choice for the reduction of sarcopenia and dynapenia, contributing to the improvement of health and quality of life among older adults. In addition, the following secondary hypotheses are proposed:

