 **H1.**
*IST has a low risk of injury in older adults.*

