#### 2.2.2. Pre-Intervention Assessment

One week before starting the 16-week IST, a comprehensive baseline assessment will be performed on the selected subjects to collect baseline data. This assessment, conducted by a physical activity professional and the research group doctor, will allow for detailed monitoring and accurate assessment of the effects of the programme, including the following variables:Physiological Variables: BP and heart rate HR (Omron M3 Comfort^®^ blood pressure monitor, HEM-7134-E, Omron Healthcare Co., Kyoto, Japan) and O2 saturation (OXYM4000 pulse oximeter, Quirumed S.L.U., Valencia, Spain) will be measured. Three resting measurements will be taken per participant, using the mean as the final data.Functional Capacity:○MVIC: The MVIC of each muscle group of the IST programme will be assessed at individualised intermediate angles (determined according to anatomical structure and motor restrictions, recorded with a HALO© digital goniometer). The CIEX SYSTEM machine (Ciex Systems©, Durango, Spain) with sensors and Chronojump software (Chronojump Boscosystems^®^, Barcelona, Spain) will be used for instantaneous measurement and visualisation of strength, tools also used in all IST sessions and for monitoring purposes.○Static Posture Assessment: Participants will be photographed in anatomical position (frontal and sagittal planes) with a Casio Exilim Pro EX-F1 camera (configuration: level tripod, lens at umbilical height, at 4 m, optical zoom, aperture priority, focal length 50 mm, f5.6, ISO 200) [81]. An analysis of documented validity and reliability for postural analysis will be performed with Kinovea^®^ software (v.0.9.x+) [82,83]. Adhesive markers or direct image identification may be used for key anatomical points [84] (sagittal: tragus, C7, acromion, greater trochanter, lateral femoral epicondyle, peroneal malleolus; frontal: acromions, anterior superior iliac spine (ASIS), posterior superior iliac spine (PSIS), patellar centre, tibial malleoli). Postural parameters will be calculated from these points (sagittal: head-neck alignment (HNA) [82], shoulder alignment, estimated spinal curvatures, pelvic tilt [84], knee alignment; frontal: head tilt/symmetry, shoulder height, pelvic symmetry [81], lower limb alignment [82]). Angles (degrees) and distances (cm/mm, after calibration if size reference is used) shall be recorded. Pre-post change will be an outcome of interest. Image analysis shall be performed, if possible, by a blinded assessor (see Section 2.1.3) [83].HRQoL: The EuroQol EQ-5D-5L questionnaire (5 items, 5 dimensions, 5 response levels) will be used [85,86]. This instrument includes two parts: a descriptive system comprising five dimensions (mobility, self-care, usual activities, pain/discomfort, anxiety/depression), each with five response levels, and a VAS where participants rate their overall health.Applicability of the IST Protocol (scales administered post-intervention):○Safety (H1): Assessed by: (1) Analysis of Adverse Events (AEs) (incidence, type, severity, relationship to IST) over 16 weeks (procedures detailed in Section 2.4.3); ‘low risk’ if the incidence of IST injuries is minimal. (2) Perceived Safety: 5-point Likert scale (1 = extremely unsafe, 5 = extremely safe) post-programme, with face validity and based on similar approaches [87]; a mean score ≥ 4 will be expected.○Acceptability (H2): Assessed by compliance rates (≥90% sessions) and overall satisfaction (5-point Likert scale: 1 = extremely dissatisfied, 5 = extremely satisfied) post-programme, using validated measures [88]; a mean satisfaction score ≥ 4 will be expected.○Difficulty (H3): Assessed with a 5-point Likert scale on perceived challenge (1 = not challenging at all, 5 = extremely challenging) post-programme, validated approach [89]; a mean score ≤ 2 will be expected.Genetic Analysis: Saliva samples will be collected using buccal swabs (4N6FLOQSwab, Life Technologies, Waltham, MA, USA). DNA will be extracted from these samples (QIAmp DNA Mini kit, Qiagen, Venlo, The Netherlands) and subsequently quantified (Qubit, Life Technologies). Genetic polymorphisms, specifically Single Nucleotide Polymorphisms (SNPs) and Insertions/Deletions (INDELs), will be analysed in genes associated with the response to strength training, hypertrophy, and strength gains [63,64,65,66,67,68,69,71,72,73]. Specifically, genes linked to the following will be analysed:○Muscle fibre typology: such as ACTN3 (R variant associated with a higher proportion of type II fibres, crucial for strength/power and affected by sarcopenia/dynapenia in ageing) [63,64].○Response to training: including ACE [63,65,66], NRF2, CKMM, MCT1, AMPD1, and the co-activators PPARGC1A and PPARGC1B (involved in mitochondrial biogenesis and exercise adaptation).○Muscle fibre damage and regeneration: genes such as IGF2, MLCK, CASP [72], MMP3 [72], TNC and GDF5 [73], which influence the response to exercise microtrauma and its repair. Moderate exercise-induced muscle damage (EIMD), potentially triggered by IST at long angles, is considered to contribute to remodelling and adaptation.○Vascularisation: NOS3 and VEGFA [67,69], essential for oxygen/nutrient supply, muscle growth and recovery, optimising metabolic stress and hypertrophic response.○Inflammation: TNF-α, CRP [60], IL-6 [60] and IL6-R, which are relevant because inflammation contributes to sarcopenia and modulates the anabolic response [70].○Oxidative damage response capacity: SOD2 [71], CAT and GPX, crucial for muscle recovery and adaptation to training stress.○Fat and carbohydrate metabolism (nutrigenomic factors): Polymorphisms in FABP2, ADRB2, ADRB3, FAT/CD36, UCP2, GCKR, ADCY5 and GIPR, which may influence nutrient uptake and hypertrophic response [74,75,76].

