#### 2.3.2. Analysis Strategy

Primary and secondary quantitative variables will be compared pre-post with Student’s *t*-tests for related samples, after testing for normality (Shapiro-Wilk). If the data are not normally distributed or contain outliers, non-parametric tests (e.g., the Wilcoxon signed-rank test) will be employed. Effect sizes (Cohen’s d) and confidence intervals will be calculated. Multivariate analyses will include a multiple linear regression to explore the influence of genetic and environmental variables on strength and muscle mass improvement, with Bonferroni correction for genetic analyses. Qualitative variables (e.g., sarcopenia diagnosis) will be analysed by using McNemar tests. Applicability variables (Likert scales, adverse events) will be analysed with descriptive statistics and *t*-tests or Wilcoxon tests for pre-post comparisons on Likert scales. Additionally, exploratory subgroup analyses will be performed to assess whether the response to IST on primary variables differs according to sex, age ranges (70–79 vs. ≥80 years) and baseline severity of sarcopenia/dynapenia. Adjustment for baseline covariates will be considered in regression models. The software will be IBM SPSS v29.0 and R v4.3.1.

For the assessment of the secondary hypotheses concerning the applicability (Section 2.2.2) of the IST protocol, specific analyses will be carried out:

Hypothesis H1 (low injury risk): This will be assessed through two approaches. First, Adverse Events (AEs) will be recorded (including their type, severity, and causality), and ‘low risk’ will be inferred if the incidence of IST-related injuries is minimal and comparable to or lower than rates reported in the literature for strength training in older adults [1,33,34,35]. Second, Perceived Safety will be measured post-intervention using a 5-point Likert scale; the approach for this subjective scale is based on similar methods used in previous research [87]. The hypothesis will be supported by a mean score of ≥4.

Hypothesis H2 (high acceptance): This will be assessed by: (1) compliance rate, with a success threshold of ≥90% of completed sessions, and (2) a satisfaction score from a 5-point Likert scale administered post-intervention, using a validated measurement approach [88]. The hypothesis will be supported by a mean satisfaction score of ≥4.

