The benefits of this IST protocol on strength and muscle mass are expected to be due to combined neuromuscular mechanisms. Neurally, 100% ME seeks to maximise the activation and firing rate of high-threshold motor units, following Henneman’s principle [32]. Muscularly, the mechanical strain of long, high-intensity isometric contractions is a potent stimulus for protein synthesis and hypertrophy [42,43,44,45]. Gradual progression of intensity and duration will facilitate these adaptations. Metabolic stress from vascular occlusion may contribute to this, and the choice of intermediate angles, in addition to safety, aims to optimise the generation of active tension by favouring a greater number of actin-myosin cross-bridges.

Several studies have shown that IST can significantly increase muscle strength and hypertrophy [42,43,44,45], positioning it as an effective tool, possibly more so than TRT, to combat sarcopenia and dynapenia in the elderly.

Beyond the technical complexity, TRT with explosive execution and high loads increases the risk of injury [33,34,35]. In contrast, IST is used in rehabilitation and special populations [36,37,38,39] because it allows safe strength work with minimal or no pain in specific ranges [36,37]. This is a practical advantage for older people with joint pain, as strengthening without exacerbating pain improves viability and can have acute analgesic effects [57,58], improving quality of life. The lower likelihood of severe DOMS and lower perceived technical difficulty may also favour acceptance of and adherence to IST.

One consideration in high-intensity IST is an acute BP response. Although maximal isometric contractions may transiently elevate BP [80,91], our protocol seeks to mitigate this risk by including participants with controlled hypertension, gradual progression of intensity, instruction for continuous breathing (avoiding prolonged Valsalva) [78,79], and constant monitoring.

Therefore, IST could be considered a safer and more effective alternative to TRT in older adults to improve their quality of life.

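### The trainer's routine question covers only unusual complaints and the low-risk rule counts only injuries, so the rule is too narrow to support a general statement that IST is safe

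*Protocol article*

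**What the plan says.** **Collection.** Under Section 2.4.3, "the trainer will actively ask about unusual complaints or symptoms (requested AEs" at each training session. The same paragraph adds an unsolicited route: "Participants will be instructed to spontaneously report any AEs between sessions to the principal investigator or trainer. All AEs will be systematically recorded". The Introduction says that "potential discomfort or adverse events will be carefully monitored", and Section 2.1.2 says supervision will watch for signs of discomfort during the exercises.

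**Outcome.** Section 2.2.1 lists AEs as a secondary outcome covering incidence, type, severity and causality, summarised as counts and percentages over weeks 1 to 16. It describes this as the objective safety profile and says it provides data to test H1.

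**Hypothesis.** H1 reads: "IST has a low risk of injury in older adults".

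**Decision rule.** Section 2.2.2 opens the item with "Safety (H1): Assessed by: (1) Analysis of Adverse Events (AEs" and goes on to call the risk low "if the incidence of IST injuries is minimal". Section 2.3.2 says this conclusion "will be inferred if the incidence of IST-related injuries is minimal and comparable to or lower than rates reported in the literature"; the literature meant is that on strength training at older ages. A second limb in both sections looks for a mean perceived-safety score of at least 4 on a 5-point scale after the programme.

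**The concern.** The Introduction asks whether IST is effective, safe and applicable, and lists safety among the objectives. H1 is the only place where the plan attaches a criterion to safety, and two features make that criterion narrower than the question.

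First, the one prompt the trainer must give is restricted to what is unusual. Pain or soreness that the trainer or participant regards as a normal result of maximal effort may not be mentioned, and the article does not say whether such expected complaints are AEs. The trainer, who is not blinded, delivers the intervention and asks the question.

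Second, the low-risk rule looks only at injuries. The protocol itself mentions harms that are not plainly injuries: an acute blood-pressure response (Discussion), exercise-induced muscle damage (Section 2.2.2 and Discussion), and unresolved mild discomfort, which is managed through the discontinuation criteria (Section 2.1.2). Such an event could be recorded as related, even as serious or as the reason for withdrawal, and not count against low risk.

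At stake is a report that says IST is safe on the strength of an injury count.

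**Working it through.** The point rests on the text. The arithmetic only shows scale.

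1. **Breadth at each step.**
   - Objective (Introduction): safety in general.
   - Solicited question (2.4.3): unusual complaints or symptoms.
   - Unsolicited reports and recording (2.4.3): any AE, all recorded.
   - Outcome said to test H1 (2.2.1): all AEs by type, severity and causality.
   - H1 as worded: risk of injury.
   - Low-risk rule (2.2.2 and 2.3.2): IST-related injuries only, with no definition of injury and no number for minimal.

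   The rule agrees with the wording of H1. It is narrower than the objective and than the outcome said to test it. Collection is broad on paper, but only part of it is prompted.

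2. **Denominator.** Section 2.3.1 gives d = 0.80, 80% power and two-sided alpha 0.05. With the noncentral t distribution for a paired test, n = 14 gives 79.0% power and n = 15 gives 82.1%, so 15 is reproduced. Allowing for 15% losses, 15/(1 − 0.15) = 17.6, rounded up to 18, which is also reproduced. The trainer's question would be put at up to 2 × 16 × 18 = 576 sessions.

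3. **What the injury limb can show.** With no injuries in n participants, the exact two-sided 95% upper limit is 1 − 0.025^(1/n). For n = 18 this is 18.5%, and for n = 15 it is 21.8%.

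4. **Non-injury events (illustration; the count is assumed).** Suppose 3 of 18 participants have a related AE that is not an injury. The proportion is 3/18 = 16.7%, with an exact (Clopper-Pearson) 95% interval of 3.6% to 41.4%. The injury count is still 0 of 18, so the first limb sees nothing. If the true proportion were 10%, 30% or 50% (assumed), the expected numbers would be 1.8, 5.4 or 9.0 of 18, and the injury count could be zero in each case.

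5. **Elicitation (illustration; both inputs are assumed).** Observed proportion = true proportion × share volunteered. With a true 30% and between 25% and 75% volunteered, the observed proportion is 0.30 × 0.25 = 7.5% to 0.30 × 0.75 = 22.5%. With a true 50% it is 12.5% to 37.5%. The documents give no basis for choosing among these values.

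6. **Perceived safety as a backstop (illustration; scores are assumed).** If 14 participants score 5 and 4 score 1, the mean is (14 × 5 + 4 × 1)/18 = 74/18 = 4.11, which still meets the threshold. The scale is given only at week 17, and under Section 2.1.2 participants who stop training continue assessments only if they wish and if it is feasible, so some who were harmed may be absent from the mean.

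**The case against.** The strongest reply is that nothing is hidden and that the rule fits its hypothesis. H1 concerns injury, and a rule that counts injuries tests it directly. All AEs are recorded and tabulated by severity and causality as a separate outcome, reasons for withdrawal are documented, and the perceived-safety score gives painful or frightening events a way to count. The word unusual limits only the prompt: participants may report any AE, sessions are individually supervised, discomfort is watched for, and new joint pain could well be called unusual by the person who has it. The exact symptom list is also detail that a condensed article may leave to the case report form.

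Most of this stands, and it rules out two stronger readings. A reader might infer that expected pain is shut out of the safety data. The documents do not support that, because the unsolicited route and the recording rule admit it; it is only less reliably elicited. A reader might also infer that the rule misstates H1, or that low risk could be declared with other harms concealed. Neither follows, since the rule matches H1 and the other harms would be reported. Nor can one argue that the Discussion's expectation of little pain would be confirmed by default: the plan has no pain outcome or hypothesis to confirm.

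What the reply does not answer is that Section 2.2.2 labels the injury rule as the assessment of safety, and Section 2.2.1 says all AEs test H1, while the criterion uses only a subset. Watching for signs of discomfort is not the same as asking, and the perceived-safety mean is a weak and indirect route.

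**Conclusion.** The concern holds in a limited form. Expected complaints are less reliably elicited than unusual ones. Related non-injury AEs, SAEs and withdrawals for AEs are tabulated but do not bear on the low-risk conclusion, except indirectly through perceived safety. The injury rule is adequate for H1 as worded; it is not adequate as the basis for saying that IST is safe.

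The size cannot be derived from the documents. The effect of the narrow prompt, where there is one, is towards fewer recorded events. This assumes that people volunteer some complaints less readily than they report them when asked, and that at least some exercise pain would be regarded as usual. The primary efficacy analyses are not affected. It is a modest fault of wording and measurement, worth correcting because the correction is cheap.

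**What to change.** - **Section 2.4.3:** ask the same open or fixed question at every session and at week 17 about any new or worse symptom, whether or not it is expected from the exercise. Extend the AE time point in Section 2.2.1 to include the week 17 question.
- **Sections 2.2.2 and 2.3.2, H1:** keep the injury criterion and its comparison with the literature, and say that the conclusion concerns injury only.
- **Sections 2.2.2 and 2.3.2, safety:** base any statement that IST is safe on the number and proportion of participants with any IST-related AE by severity, with SAEs, and with withdrawal for an AE, each with an exact 95% interval. Report injuries as one category among these.

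The cost is rewording in these sections and a line or short list on the existing case report form. The trainer already asks a question at each session, so no new contact is needed except the question at the week 17 visit. The downside is that more mild AEs will be recorded and the safety figure will look less favourable. The change concerns measurement and reporting only; it sets no rule on training, progression or discontinuation.
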